### Clinical and morphological parameters

Following parameters will be collected in the prospective database: Basic characteristics (age, sex etc.), date of admission, timing of operation, timing of seizure, date of discharge, pupil status (isocor, anisocor, wide), operative treatment, comorbidities (arterial hypertension, cardiac disease,,respiratory disease, hematological disease, renal disease, infection, oncological disease etc.), anticoagulation, antiplatelet treatment, radiological parameters (volume of hematoma, midline shift, stroke,) GCS at admission/discharge/follow-up, GOS/mRS at discharge/follow-up and complications (bleeding, infection etc.).

### Adverse events

In a previous study by Johnston et al., the following complications of invasive subdural electrode monitoring in 112 children were described: wound infection (2.4%), cerebrospinal fluid leak (1.6%) and subdural hematoma, symptomatic pneumocephalus, bone flap osteomyelitis, and strip electrode fracture (each 0.8%). In contrast to this study, the complication rate in our study should be lower since we only used subdural strip electrode, that are smaller with limitation to four to six contacts, and less invasive than extended and multiple grid electrodes, furthermore the procedure will be performed only in patients with planned craniotomy/craniectomy [12].

In summary, serious adverse events will be recorded in the database and will include any of the following: intracerebral hemorrhage after removal of the electrode, infection or wound healing impairment requiring antibiotic treatment, death, and life-threatening events caused by the subdural EEG electrode. In these cases, the electrode will be removed and the observed adverse events will be reported to the local ethics committee.

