**Methods:**

In a prospective nonrandomized trial, we aim to include 110 patients with aSDH. Only patients undergoing surgical removal of aSDH will be included; one arm will be treated according to the guidelines of the Brain Trauma Foundation, while the other arm will additionally receive a subdural grid electrode. The study’s primary outcome is the comparison of incidence of seizures and time-to-seizure between the interventional and control arms. Invasive therapeutic monitoring will guide treatment with antiseizure drugs (ASDs). The secondary outcome will be the functional outcome for both groups as assessed via the Glasgow Outcome Scale and modified Rankin Scale both at discharge and during 6 months of follow-up. The tertiary outcome will be the evaluation of chronic epilepsy within 2–4 years of follow-up.

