### Trial interventions

The surgical procedure is standardized for both arms. All patients with aSDH will undergo the surgical evacuation of hematoma via craniotomy or craniectomy and receive subdural drain as well as an intracranial pressure monitoring probe. One arm would additionally receive a subdural EEG electrode with continuous monitoring (intervention arm), while the other arm would be treated with the standard treatment (control arm) according to the guideline from Brain Trauma Foundation as follow:

Treatment:
Hyperventilation only as a temporizing measure to reduce ICP with maximum PaCo2 of 30 mmHg (evidence IIb)Barbiturate administration only to control elevated ICP refractory to maximum standard medical and surgical treatment (evidence IIb)Early tracheotomy in case of inadequate recovery (evidence IIa)Feeding patients to attain basal caloric replacement at least by the fifth day (evidence IIa)Low molecular weight heparin for the deep vein thrombosis prophylaxsis

Monitoring:
Intracranial pressure monitoring (<22 mmHg) (evidence IIb)Cerebral perfusion pressure monitoring (60-70 mmHg) (evidence IIb)Systolic blood pressure >100 mmHg (evidence III)

The subdural EEG electrode (PLATIN 1 × 4 or 1 × 6; Ad-Tech Medical Instrument Corporation, Oak Creek, WI, USA) will be intraoperatively implanted in the subdural space frontotemporally and diverted separately from the wound area (Fig. 2). Next, a postoperative CT scan will be performed and all patients will be monitored in the intensive care unit (Fig. 3).

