**Fig. 3 Fig3:**
[figure not shown]
**a** Postoperative scout of CT scan with frontal EEG electrodes. **b** Coronary reconstruction of the CT scan. **c** Postoperative scout of CT scan with temporal EEG electrodes. **d** 3D reconstruction of the CT-scan

As a clinical parameter, GCS will be evaluated every day and surface EEG will be performed at least once during the first 7 days post-operation in all patients. Additional surface EEGs will be performed if there is a suspicion of seizure. In the intervention arm, the continuation of invasive EEG monitoring will be evaluated by a board-certified epileptologist (Fig. 4). If a seizure is detected on EEG, treatment with benzodiazepines and ASDs will be started under further EEG monitoring and in consideration of the patient’s clinical condition. Treatment with ASDs will be adjusted on demand according to clinical and EEG assessment. If treatment with benzodiazepines and intravenous ASD is deemed insufficient for seizure suppression, escalation of treatment with anesthetics to obtain a seizure suppression or burst suppression pattern under EEG monitoring would be considered. The maximum period of invasive monitoring is set at 7 days, at which point the electrode should be removed. The subdural EEG electrode is removed simply by drafting as a normal wound drain and the incision sutured with Premilene 3.0 (Braun Melsungen AG OPM, D-34212 Melsungen, Germany).

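### The serious adverse event definition ties life-threatening events to the electrode and names no harm from the EEG-guided seizure treatment, although that treatment is part of the tested strategy

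*Protocol article*

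**What the plan says.** The Adverse events section of the protocol article states that "serious adverse events will be recorded in the database and will include any of the following". The items are "intracerebral hemorrhage after removal of the electrode, infection or wound healing impairment requiring antibiotic treatment", followed by "death, and life-threatening events caused by the subdural EEG electrode". The consequence is the same for every item: "In these cases, the electrode will be removed and the observed adverse events will be reported to the local ethics committee".

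The treatment that follows from the monitoring is described in the Trial interventions section, in the text after Fig. 3: "If a seizure is detected on EEG, treatment with benzodiazepines and ASDs will be started under further EEG monitoring". If that is not enough, "escalation of treatment with anesthetics to obtain a seizure suppression or burst suppression pattern under EEG monitoring would be considered". The Methods paragraph of the Abstract presents this as part of the design: "Invasive therapeutic monitoring will guide treatment with antiseizure drugs (ASDs".

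The Trial outcomes measures section has one secondary outcome for the effects and benefits of the invasive monitoring together with the treatment it leads to, and another for the intervention's complication rate. The second is not defined further. The database list under Clinical and morphological parameters has an open-ended complications item, with bleeding and infection as its examples.

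**The concern.** The strategy under test has two parts: an electrode that finds seizures, and drug treatment that is started and escalated on what the electrode shows. The Background section of the Abstract describes it this way, as implanting, diagnosing, treating under monitoring and then analysing clinical benefit. The serious event list was evidently written for the first part only. The attribution clause limits life-threatening events to those the electrode causes, and the prescribed response is to take the electrode out.

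The result is an uneven account. Treatment prompted by the monitoring is expressly counted where it may help and is not expressly counted where it may harm. Two things are at stake:

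- **Oversight.** The ethics committee could miss a pattern of serious treatment harm, because such events are not on the list that triggers a report.
- **Comparison.** The article aims at a standard treatment guideline, which needs harm measured in the same way in both arms. A definition that refers to the electrode cannot do that for patients who have none.

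**Working it through.** There is no stated figure to reproduce. The point rests on reading the sections together, plus one multiplication.

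**Step 1. Test each listed item against a serious drug or anaesthetic event.**

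| Listed item | Attributed to the electrode? | Would seizure-treatment harm qualify? | Possible in controls? |
|---|---|---|---|
| Haemorrhage after electrode removal | Yes | No | No |
| Infection or impaired wound healing needing antibiotics | Not explicitly | Only if it takes that form | Yes |
| Death | Unclear; the clause may or may not reach it | Yes, if read as death from any cause | Yes, if read as death from any cause |
| Life-threatening event | Yes | No | No |

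A life-threatening drug or anaesthetic event that the patient survives, and that is not an infection, meets none of the four. Two of the four cannot arise in a control patient.

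**Step 2. Ask whether the treatment belongs to the strategy.** The Abstract says that monitoring guides drug treatment. The Trial interventions section makes an EEG-detected seizure the trigger for drugs and lists anaesthetic escalation as an option. The benefit outcome names the monitoring and the resulting treatment together. All three point the same way.

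**Step 3. Size the group concerned.** Inputs from Statistical analysis and sample size: an assumed difference in incidence of 20%, and 55 patients per arm.

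- Read as percentage points: 0.20 × 55 = 11 more intervention patients with a detected seizure. This holds whatever the base rate.
- As an illustration of levels, take the 28% mean incidence from the Background as the control rate: 0.28 × 55 = 15.4 and 0.48 × 55 = 26.4, difference 11. The article does not name 28% as its planning rate.
- If the 20% were relative, on the same 28%: 0.20 × 0.28 × 55 = 3.1 more patients.

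**Step 4. Ask what this means in events.** The documents give no risk of serious drug harm. For illustration only, an assumed risk of 2% to 20% per treated patient gives 11 × 0.02 = 0.22 to 11 × 0.20 = 2.2 expected events among those 11 patients. This is not a net difference between arms, because drug exposure in controls is not known.

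**The case against.** The best defence has four parts.

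1. **The list is not purely about the electrode.** A reader might infer that it covers electrode harm alone and that no treatment harm can count. The text does not support that. Death may be read as death from any cause, and the infection item carries no explicit attribution. This stands, and it is why the point is confined to non-fatal, non-infectious harm.
2. **The list is not declared exhaustive, and other data exist.** The wording says that events will include those named. The open-ended complications item could pick up some drug harm, and the functional outcomes in both groups would reflect harm that worsens recovery. So a reader who concludes that treatment harm is left out altogether goes too far. But a complications field does not make an event serious or reportable, and a functional score does not identify its cause. The article may leave detailed reporting rules to a fuller document, but it states this definition itself, with an attribution clause that narrows it.
3. **More treatment is not the stated aim.** A reader might infer that the trial is designed to increase drug or anaesthetic use. The documents support more detection and hence more treatment starts, but anaesthetics are only to be considered. The Discussion even presents early detection as a way to avoid complications of prophylaxis. Controls follow a guideline that, according to the Background, recommends first-week prophylaxis in severe brain injury, while the treatment list under Trial interventions does not mention it. Control exposure is therefore undetermined, and no net excess of drug harm can be claimed.
4. **A device-focused list is a defensible choice in a trial described as phase I.** The arms differ by the electrode and its monitoring, and the drugs are not called investigational. That would carry weight if the outcomes were also confined to the device, but the benefit outcome includes the resulting treatment.

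**Conclusion.** The concern holds in a limited form. As written, the definition does not list serious harm from EEG-guided seizure treatment unless it is fatal or takes the form of an infection or wound problem needing antibiotics. The resulting list cannot support a like-for-like comparison of harm between arms. At best the wording is ambiguous, and that ambiguity sits in the rule that decides what the ethics committee sees.

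On the percentage-point reading of the protocol's 20%, about 11 of 55 intervention patients are the additional group to whom this applies. That figure assumes that the planned difference occurs and that each additional detected seizure leads to treatment as the Trial interventions section describes. How many events would go unlisted is unknown. The primary outcome is not affected. The issue concerns safety reporting and the balance of the secondary outcomes, and it should be corrected because the remedy is cheap.

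**What to change.** Reconcile the Adverse events, Trial interventions and Trial outcomes measures sections:

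- Define a serious event by its seriousness (death, life-threatening, or otherwise serious) without requiring that the electrode caused it, and say plainly that death means death from any cause.
- State that serious events related to seizure treatment with benzodiazepines, antiseizure drugs or anaesthetics are included for recording and for reporting to the ethics committee.
- Record events by the same definition in both arms, with suspected relation to the electrode or to seizure treatment as a separate item.
- Report the complication-rate outcome for the whole strategy by arm, with device-related events as a subset.
- State separately which events lead to electrode removal. At present one sentence ties removal to every listed event, so a wider definition would extend that rule unintentionally. Which events should trigger removal is a clinical decision for the sponsor.

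Values such as "Cerebral perfusion pressure monitoring (60-70 mmHg" should not be used as a ready-made harm measure. They are monitored but do not appear in the database list, and departures may come from the brain injury itself.

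The cost is revised wording, some added form fields in both arms, a few more reports to the ethics committee, and a stated complication rate that may look less favourable. Sample size and clinical care need not change.

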### Statistical analysis and sample size

The IBM SPSS Statistics version 25 software program (IBM Corp., Armonk, NY, USA) will be used for data analysis. Data will be described using means ± standard deviations and numbers of patients, including percentages for continuous and categorical variables. For parametric parameters, an unpaired t-test will be used. For nonparametric parameters, variables will be analyzed in a contingency table using either Fisher’s exact test or the chi-squared test as appropriate. To assess the impact of the variables, odds ratios with 95% confidence intervals will be calculated. A *p*-value of 0.05 or less is considered to be statistically significant and all tests will be two-tailed.

When estimating the sample size with consideration of increased seizure detection by invasive EEG monitoring, the difference in the incidence rate is assumed to be 20%. The sample size was calculated as 110 patients (*n* = 55 patients each arm) to ensure 80% power (1-ß = 0.8). Moreover, time-to-event analysis will be performed to detect the timeline until seizure detection.

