## Background

Epileptic seizures are one of the frequent complications seen in patients with traumatic brain injury; the incidence is approximately 20% [1]. In particular, acute subdural hematoma (aSDH) is one of the most important predictors for seizures—alongside other parameters like age, preoperative Glasgow Coma Scale score, cerebral herniation, hematoma volume, and time to operation—associated with worse neurological outcome [2–8]. In a recent systematic review, the mean incidence of seizures in aSDH was 28%, whereas one retrospective study focusing on diagnostic electroencephalography (EEG) reported a very high incidence of epileptiform discharges on surface EEG scans in 87% of patients with aSDH. Thus, the question arises as to whether the incidence of seizures is underestimated [8, 9].

Despite the successful evacuation of subdural hematoma, approximately one third of patients show no clinical improvement without any medical explanation as to why. Surface spot EEG is routinely performed to detect seizures; however, the sensitivity of this approach is limited due to the skin–bone barrier and the short duration of recording. Furthermore, surface EEG is not always available as a diagnostic tool—for example, during the night or on weekends—which is an additional limitation leading to lengthier time to treatment. Spot surface EEG only records for 20 to 30 min in contrast with continuous EEG recordings which are performed for hours or days.

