## Methods/design

### Trial design

This is a prospective nonrandomized controlled study (phase I trial) where eligible participants will be divided into two arms: one intervention arm and one control arm. Enrollment, allocation, analysis and follow-up were summarized as a flow chart (Fig. 1).

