### Study setting and inclusion/exclusion criteria

Patients will be recruited from the Department of Neurosurgery, University Hospital Frankfurt am Main following a diagnosis of aSDH. The local neurosurgical teams review patients upon admission and will assess eligibility for inclusion in the DISEASE trial. If informed consent is obtained and a mobile EEG system is available for recording, patients will be recruited into the intervention arm. Otherwise (e.g., a mobile EEG system is not available because it is already in use for the recording of other patients), patients will be placed in the control arm for follow-up.

This study will include adult patients (aged ≥18 years) with symptomatic aSDH requiring operative treatment via craniotomy or craniectomy who provided informed consent. Patients with infaust prognosis, asymptomatic patients with conservative treatment, those with aSDH as a secondary diagnosis, and those with concurrent enrollment in any other trial will be excluded.

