Previously, several studies have been investigating the benefit of a continuous scalp EEG monitoring in patients with TBI [21, 22]. Struck et al. performed a prospective multicenter study analyzing over 5000 EEGs performed on over 4700 participants [21]. Hereby, 6 variables in EEG pattern could be identified creating a simple 2HELPS2B score system. Furthermore, this score system could be validated in other multicenter studies giving a robust basis for seizure prediction by EEG [21, 22]. We have no doubt that the continuous scalp EEG might be an inevitable future tool for seizure monitoring in TBI, still the invasive EEG has its advantage on the recorded hemisphere wherefore both monitoring could potentiate the sensitivity and specifity of seizure diagnostic. While preliminary results have been quite promising regarding detection rate and timing of seizure, questions of clinical benefit are still unanswered. This study expects to contribute to the validity of an important novel standard treatment for patients surgically treated for aSDH or traumatic brain injury in the future.

Potential limitations to this study include reaching an adequate recruitment number in the interventional arm, since aSDH is mostly an emergent situation where informed consent often cannot be obtained in a timely manner or at all. To overcome this limitation, an independent physician can also consent on behalf of a patient. Furthermore, the interventional and the control arm are not randomized due to the limited capacity of invasive, continuous EEG recording device. Therefore, there might be some bias in the selection criteria, however, we tried to overcome it by allocating every patient into interventional arm if the EEG recording device was available for use. Finally, this study is deployed only in a single center; however, after the phase I trial, we hope to conduct a multi-center prospective randomized trial to develop evidence-based recommendations for invasive subdural EEG monitoring in case of traumatic brain injury in general.

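### The arms are not randomised and selection bias is conceded, yet the between-arm tests named are unadjusted; the comparisons, above all GOS/mRS, are open to confounding

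*Protocol article*

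**What the plan says.** - **Design.** Protocol article, Trial design: "This is a prospective nonrandomized controlled study".
- **Allocation.** Study setting and inclusion/exclusion criteria: "If informed consent is obtained and a mobile EEG system is available for recording, patients will be recruited into the intervention arm". Otherwise, "patients will be placed in the control arm for follow-up". The example given for control placement is a device already in use for other patients.
- **Acknowledged bias.** Discussion: "Therefore, there might be some bias in the selection criteria". The only remedy offered is the allocation rule itself, under which every patient goes to the intervention arm when a device is free.
- **Tests.** Statistical analysis and sample size: "For parametric parameters, an unpaired t-test will be used"; categorical data go into contingency tables with Fisher's exact or the chi-squared test. Odds ratios with 95% confidence intervals and a time-to-event analysis are also announced, without a model for either.
- **Prognostic factors.** Besides aSDH itself, the Background lists "age, preoperative Glasgow Coma Scale score, cerebral herniation, hematoma volume, and time to operation".
- **Data collected.** Clinical and morphological parameters lists age, date of admission, timing of operation, pupil status, GCS at admission and "radiological parameters (volume of hematoma, midline shift, stroke", among others.

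**The concern.** A t-test or a two-by-two test reads a difference between arms as a treatment effect only if the arms are otherwise comparable. Randomisation would make them so in expectation, and this design does not have it. The allocation rule has two parts. Device availability may well be unrelated to prognosis. Timely consent may not be, because the Discussion says that in this emergency setting consent often comes late or not at all, and that can depend on how ill the patient is.

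The stake is highest for GOS/mRS. The Discussion leaves clinical benefit as the open question, functional outcome is where it would show, and the Background ties the listed factors to neurological outcome. If one arm has older patients, lower GCS or larger haematomas, a crude comparison would credit or charge the difference to the electrode. This goes beyond a detail left to a separate analysis plan, because the article itself names the tests and they do not suit the design.

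**Working it through.** **1. What is adjusted and what is not.** The t-test, Fisher's exact test and the chi-squared test are unadjusted by construction. For the odds ratios and the time-to-event analysis no method is stated, so they may or may not be adjusted. No covariate, stratification, matching or weighting appears anywhere in the article.

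**2. Which listed factors are available.**

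| Background | Data list |
|---|---|
| Age | Age |
| Preoperative GCS | GCS at admission |
| Haematoma volume | Haematoma volume |
| Time to operation | Timing of operation, with date of admission |
| Cerebral herniation | Not named; pupil status and midline shift are proxies |

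Four of five are collected by name or near equivalent.

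**3. Possible size.** The plan gives no figure for imbalance or bias, so there is none to reproduce. From the document come only n = 55 per arm, two-sided 0.05, and the 28% seizure incidence in the Background. The rest is assumed: one binary factor with overall prevalence 50%, an odds ratio of 3 for seizure, an odds ratio of 4 for good function with a 40% mean rate, and no true arm effect.

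Let r0 and r1 be the risks without and with the factor, set so that (r0 + r1)/2 equals the mean risk and the odds ratio is as assumed.

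- Seizure: r0 = 17.35%, r1 = 38.65%, r1 − r0 = 21.3 points.
- Good function: r0 = 24.1%, r1 = 55.9%, r1 − r0 = 31.8 points.

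False difference d = (r1 − r0) × (difference in factor prevalence between the arms). SE = √[(pA(1 − pA) + pB(1 − pB))/55]. Type I error = P(Z > 1.96 − d/SE) + P(Z < −1.96 − d/SE).

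| Outcome | Imbalance | Arm risks | d (points) | SE | d/SE | Type I error |
|---|---|---|---|---|---|---|
| Seizure, OR 3 | 65/35 | 31.2% / 24.8% | 6.4 | 0.0854 | 0.75 | 11.6% |
| Seizure, OR 3 | 60/40 | 30.1% / 25.9% | 4.3 | 0.0855 | 0.50 | 7.9% |
| Seizure, OR 3 | 55/45 | 29.1% / 26.9% | 2.1 | 0.0856 | 0.25 | 5.7% |
| Function, OR 4 | 65/35 | 44.8% / 35.2% | 9.6 | 0.0930 | 1.03 | 17.7% |
| Function, OR 4 | 60/40 | 43.2% / 36.8% | 6.4 | 0.0932 | 0.68 | 10.5% |
| Function, OR 4 | 55/45 | 41.6% / 38.4% | 3.2 | 0.0934 | 0.34 | 6.3% |

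At 60/40 to 65/35 the range is about 8% to 18%; at 55/45 the error is close to nominal. The bias can run in either direction.

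**4. How many covariates the data carry.** The control seizure rate behind the sample size is not stated. Assuming 28%, and 48% with the planned 20-point difference, the expected number of events is 55 × (0.28 + 0.48) = 41.8. Arm plus three covariates gives 41.8/4 ≈ 10 events per term; arm plus four gives 41.8/5 ≈ 8. The list must be short.

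**The case against.** **Allocation may be close to haphazard.** The only example of control placement is an occupied device. The inclusion criteria and the Timeline suggest that consent is sought in both arms, and a representative or independent physician may consent. If arm is unrelated to prognosis, a split as uneven as 60/40 in a factor of 50% prevalence has a probability of about 3.6% (0.20/0.0953 = 2.10 standard errors), and 65/35 about 0.2% (0.30/0.0953 = 3.15). This stands as a reason for caution. A reader might infer that the comparisons are confounded; the document shows only that they are open to it. The allocation text still makes consent a condition of the intervention arm and sends everyone else to control, so the consent route is not closed.

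**Not every analysis is shown to be crude.** A reader might infer that all between-arm analyses are unadjusted, or that the predictors of seizures will rest on crude odds ratios pooled over arms. The text does not say so: logistic or Cox regression would fit its wording for the odds ratios and the time-to-event analysis. The point therefore rests on the three named tests.

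**Not every factor is collected.** Herniation is not a named item, and time to operation depends on how precisely admission is recorded. The Background sentence also leaves open whether its factors predict seizures, worse neurological outcome or both, so the odds ratio of 3 for seizure has no support in the text.

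**Adjustment leaves the larger problem for seizures.** Continuous invasive EEG for up to seven days and at least one surface EEG detect seizures differently. That is unequal ascertainment, which baseline covariates cannot correct. This stands in full.

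**It is a single-centre phase I study that discloses the limitation.** True, but disclosure does not change which test is run.

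**Conclusion.** The point holds in this form: non-randomised arms, a conceded risk of selection bias, and named tests that take no account of it. The between-arm comparisons are open to confounding, chiefly GOS/mRS. The size is unknown. The 8% to 18% range is an illustration that rests wholly on an assumed imbalance, prevalence and odds ratios, with no true effect; with a small imbalance the error would be near 5%. A reader should not take it as an estimate for this trial, nor conclude that every planned analysis is unadjusted or that every listed factor is available. For seizure incidence and time to seizure, adjustment addresses case mix only and leaves the detection difference as it is.

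**What to change.** In Statistical analysis and sample size:

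- Make the main between-arm comparison of GOS/mRS, and of seizure incidence and time to seizure, an adjusted one: ordinal, logistic and Cox regression respectively, or propensity-score overlap weighting.
- Fix in advance about three or four covariates, for example age, admission GCS, haematoma volume and pupil status in two levels. Use penalisation if more are wanted.
- Keep the t-test, Fisher's exact and chi-squared tests as supportive, and report standardised differences at baseline.
- Include arm in any model for predictors of seizures.
- State that adjustment does not remove the difference in seizure detection between continuous invasive EEG and spot surface EEG.

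The suggested covariates are already in the data list; herniation itself would need a new item if it is wanted. The cost is some wording, a few model fits and possibly wider intervals, mainly where the arms overlap poorly.

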### Timeline

The anticipated timeline for study participants is as follows:
Patient admission with aSDHInformed consent obtained (interventional arm/control arm)Operative treatment of hematoma via craniotomy/craniectomy either with or without placement of subdural EEG electrodeMonitoring in intensive care unitPostoperative CT control 24 h laterClinical assessment as part of the routine standard of care (e.g., GCS, neurological status, routine laboratory tests)Three to seven days of invasive EEG monitoring by a board-certified epileptologistOptional spot surface EEG, usually between Days 1 and 7Removal of subdural EEG electrode at Day 7Patient discharge after clinical evaluationOutpatient clinical evaluation at 6 months postoperatively.Evaluation of chronic epilepsy at follow-up in 2–4 years

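### The stated test rule has no rank or ordinal method, so on its natural reading mRS and GOS go to tables that ignore order or need an unstated cut-point; the functional time point is also inconsistent

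*Protocol article*

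**What the plan says.** Protocol article, Statistical analysis and sample size, gives two routes for group comparisons. The first is "For parametric parameters, an unpaired t-test will be used". The second is "For nonparametric parameters, variables will be analyzed in a contingency table", by Fisher's exact or chi-squared test. Odds ratios with 95% confidence intervals are added, and "value of 0.05 or less is considered to be statistically significant and all tests will be two-tailed". Time-to-event analysis is named only for seizure detection. The section does not say which variable takes which route.

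The sample size of 55 per arm is derived for seizure incidence alone. No power is stated for mRS, GOS or any other secondary outcome.

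Trial outcomes measures lists functional and neurological outcome (mRS, GOS) first among the secondary outcomes, at discharge and at 3 to 6 months. The Abstract (Methods) places it "both at discharge and during 6 months of follow-up". Timeline has one outpatient evaluation, at 6 months, and the end of Trial outcomes measures says that all patients have a 6-month clinic appointment, with a phone call otherwise. Clinical and morphological parameters adds GCS at admission, discharge and follow-up to the ordered scales collected.

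**The concern.** The rule treats 'nonparametric' as if it meant 'categorical'. An ordered scale such as mRS or GOS is neither normally distributed nor nominal, and the rule has no suitable place for it. In a full contingency table, chi-squared and Fisher's test give the same answer if the categories are shuffled, so the information that one grade is better than the next is lost. In a 2×2 table, the result depends on a cut-point that the protocol does not give, and differences on either side of the cut are ignored.

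The functional scales are the main patient-level evidence on whether invasive monitoring helps, a question that the Discussion calls unanswered. With 55 per arm there is little power to spare. The differing time points raise a separate issue: which assessment is the one to be compared.

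**Working it through.** **Plan's own figure.** There is none for functional outcome. The 110 patients relate to seizure incidence, where "the difference in the incidence rate is assumed to be 20" per cent, and do not bear on this point. The check therefore takes the planned arm size and asks what each candidate test would deliver.

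**Inputs from the protocol.** 55 per arm; two-sided 0.05.

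**Assumptions, as the document gives neither.** Control mRS 0 to 6 = 5, 8, 12, 15, 20, 15, 25%; common odds ratio (OR) for a better grade of 2.0 or 2.5.

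**Step 1: intervention distribution.** Multiply each cumulative control odds c/(1−c) by the OR and convert back. For mRS 0–3, c = 0.05 + 0.08 + 0.12 + 0.15 = 0.40, odds 0.667.
- OR 2.0: odds 1.333, so 0.571. All grades: 9.5, 13.5, 17.0, 17.1, 17.9, 10.7, 14.3%.
- OR 2.5: odds 1.667, so 0.625. All grades: 11.6, 15.6, 18.3, 17.0, 16.4, 9.3, 11.8%.

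**Step 2: closed-form power.**
- Ordinal (Whitehead): V = N(1 − Σp̄³)/12, power = Φ(ln OR × √V − 1.96). OR 2.0: V = 110 × (1 − 0.0253)/12 = 8.93, Φ(0.11) = 54%. OR 2.5: V = 110 × (1 − 0.0238)/12 = 8.95, Φ(0.78) = 78%.
- Dichotomy 0–3 v 4–6, chi-squared: power = Φ{(|p₁−p₂|√55 − 1.96√(2p̄q̄))/√(p₁q₁+p₂q₂)}. For 0.40 v 0.571, Φ(−0.16) = 43%. For 0.40 v 0.625, Φ(0.41) = 66%.
- Unordered 2×7 chi-squared, 6 df: non-centrality 55 × Σ(p−q)²/(p+q) = 55 × 0.0757 = 4.16, power 28%; 55 × 0.1295 = 7.12, power 48%.

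**Step 3: simulation of the same setting.**

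| Test | OR 2.0 | OR 2.5 |
|---|---|---|
| Rank test (Mann-Whitney) | 53% | 78% |
| t-test on the grades | 53% | 78% |
| Chi-squared, mRS 0–3 v 4–6 | 42% | 64% |
| Fisher, mRS 0–3 v 4–6 | 35% | 57% |
| Chi-squared, unordered 2×7 | 27% | 46% |

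Losses against the rank test are 53 − 42 = 11 and 78 − 64 = 14 points for the dichotomy, 18 and 21 for Fisher, and 26 and 32 for the unordered table. Allowing about a point of simulation error, these are ranges of 10–14, 18–22 and 25–32.

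**Step 4: other assumed distributions.** Three further mRS distributions (poor, flat, middling) give the following.
- OR 2.0: rank 51–55%, dichotomised chi-squared 40–43%, Fisher 33–35%, 2×7 26–29%.
- OR 2.5: 75–77%, 60–64%, 51–56% and 45–46%.

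Moving the cut to 0–2 v 3–6 gives chi-squared power of 35–42% and 57–64%, so the unstated cut matters. An assumed 5-level GOS at OR 2.5 gives rank 76%, dichotomised 65% and 2×5 table 55%.

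**Step 5: patients per arm for 80% power at OR 2.5** (the three further distributions). Ordinal 58; mRS 0–3 split 78–88; unordered 2×7 106.

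**Step 6: time point.** The outcome list gives 3 to 6 months; the Abstract, the Timeline and the end of the outcomes section give 6 months. Nothing in steps 1 to 5 depends on timing.

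**The case against.** **The section assigns no variable by name.** A reader might infer that the protocol sends mRS, GOS, GCS and haematoma volume to tables. It does not say so. The preceding sentence pairs means and percentages with continuous and categorical variables, so 'parametric' may simply mean continuous. Haematoma volume may then go to the t-test, and so may mRS, in which case no power is lost. This stands, and is why the point rests on the natural reading. Even so, the text leaves the reader to guess between a t-test on a scale that ends in death and a table without order.

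**The likely table is a dichotomy.** The planned odds ratios suggest a 2×2 table, which is a valid test. The 10 to 14 point loss is therefore the figure to lead with; the 2×7 loss is the outer case.

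**Detail belongs in the analysis plan.** That would excuse silence. Here a rule is stated, and an analysis plan that followed it would carry the problem forward.

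**The consequence is modest.** Functional outcome is secondary in a single-centre, non-randomised phase I study, and even a rank test has only about 53% power at an odds ratio of 2.0. This stands too: a better test does not make the comparison confirmatory, nor does it cure allocation by device availability.

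**Conclusion.** The point holds in limited form. The stated rule lacks a rank or ordinal method and, on its natural reading, discards the ordering of the main functional outcome. The cost is about 10 to 14 points of power for a dichotomised chi-squared test, about 18 to 22 for Fisher and about 25 to 32 for an unordered table, at assumed odds ratios of 2.0 to 2.5 and 55 per arm. The direction held under every distribution tried; the exact size rests on assumed distributions and a proportional-odds shift.

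The time-point conflict is a separate inconsistency to reconcile. Three stronger readings are tempting and not supported:
- That functional outcome is the only comparison of clinical benefit. Trial outcomes measures also lists therapeutic effects, including progression to status epilepticus, and chronic epilepsy.
- That the 3 to 6 month wording costs power. No such loss is shown, and all patients are scheduled at 6 months.
- That chronic epilepsy will be compared in a simple table of unequal follow-up. The Timeline has "Evaluation of chronic epilepsy at follow-up in 2–4 years", but no section says how it will be analysed.

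**What to change.** Replace the two-way rule with one that matches the type of variable:
- **Ordered scales (mRS, GOS, GCS):** proportional-odds regression, adjusted for collected baseline prognostic factors such as age, admission GCS, pupil status, haematoma volume and midline shift, because allocation is not random; or the Wilcoxon-Mann-Whitney test.
- **Clearly skewed continuous variables:** a rank test, with median and interquartile range.
- **Binary and nominal variables:** chi-squared or Fisher, as now.

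If a dichotomised mRS or GOS is also wanted, state the cut-point in advance.

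Separately, give one time point for functional outcome throughout. The 6-month visit already scheduled for all patients would serve as the analysis time point.

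The cost is wording only: the named software supports these methods and no new data or visits are needed. The small downside is a proportional-odds assumption to check, or a less direct effect measure if the rank test is chosen.
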